**Figure 2 F2:**
[figure not shown]
Archimedean spiral to be drawn with a pressure-sensing stylus on a 10.5 inch screen on an Apple iPad Touch, starting from the point in the middle.

## Methods and Anticipated Results

Acceleration data by the smartwatches will be analyzed with signal processing methods (including Fast Fourier Transform and band-pass filters) to infer average tremor amplitude and frequency in each examination section. Figure 3 illustrates a number of readily implemented graphical user interfaces and functioning initial results analyses.

**Figure 3 F3:**
[figure not shown]
Overview screen **(left)**: the full examination takes approximately 20-min and starts with questionnaires and heart frequency measurement by the smartwatch. Before hand-tremor assessment starts, smart-watch calibration is required. Questionnaire screen **(upper right)**: showing one item of the PD-NMS instrument. Initial signal processing on the smartphone **(bottom right)**: visualization of average amplitude and frequency, raw acceleration data during examination section 3 and frequency spectrum. The acceleration data illustrates a simulated case of re-emergent tremor on the time axis. FFT, Fast Fourier Transform. Data capture and analyses of tablet-based spiral drawing is not implemented yet.

Data captured by spiral drawing will be processed for angular feature detection, direction inversion and pattern deviation from ideal spiral according to Zham et al. (8). The sum of all captured and processed data will train a neural network model to predict the diagnosis label (PD, ET, none of them) and identify data patterns that could represent new biomarkers. The model will be trained applying Google Tensor Flow-based Network architectures using Convolutional neural networks (CNN) as they have shown highly promising pattern recognition results in medical images (11). In addition, long short-term memories (LSTM) networks will enable time-series analysis to account for temporal dynamics within the protocol-based examination and tablet-based spiral drawing. Both core methods (CNN + LSTM) will continuously be evaluated separately and in combination (e.g., using LSTM on top of CNN-extracted features). Sensitivity, positive predictive value/precision and accuracy will be calculated based on existent diagnosis labels using nested cross-validation. Statistical significance of classification results will be calculated by permutation tests. Univariate and Multivariate Analyses will be performed based on standard statistical regression analyses (e.g., logistic regression). This is necessary, first, to continuously and critically compare performance of Deep Learning black boxes with classical statistical approaches and second, to get a deeper understanding of the inter-related input features and their predictive power to classification results.

A concrete formulation of hypotheses is limited since we did not find any similar systems that were evaluated in studies from which we can derive a reliable patient sample size calculation based on statistical power analyses. Therefore, following key performance indicators (KPI) are aimed at the end of the study period based on classification performances in other disease domains (11, 20):
- **KPI 1:** >80% of all recruited participant cases will provide complete data as described in data capture Table S1 in the pseudonymized research database.- **KPI 2:** >90% accuracy, >90% sensitivity, >90% positive predictive value for classifying ET and PD by the tested model using nested cross validation.

All data items from smartwatch-based data and questionnaires that are relevant for data analysis are specified in the standardized Operational Data Model by the clinical data interchange standards consortium and will be available on the MDM-Portal.

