- First, there is poor integration of clinically relevant motor and non-motor phenomena. Especially, changes in tremor characteristics in relation to provoking circumstances (e.g., specific motor or cognitive actions) are currently not integrated into electronic tremor analyses. The SDS system utilizes different monitoring settings in one easy-to-follow examination at a health care facility: (A) Movement monitoring using two smartwatches at both patient wrists in a pre-defined neurological examination that provokes different tremor types. (B) Electronic questionnaires regarding medication/drug consumption, family history and non-motor symptoms on a smartphone. (C) Archimedean Spirals drawn by the patient on a tablet. Each of these three settings viewed individually already show high potential to classify or stratify tremor-related diseases (7–9). However, synchronization of these multimodal data (A–C) and advanced pattern recognition analyses such as Deep Learning would unlock a new integrative approach to boost classification performance and to find new phenotypical characteristics. In particular, Deep Learning methods have recently shown high classification performance in pattern recognition in other medical domains if a large amount of expert-tagged training data is available (10, 11).- Second, there is a lack of open data repositories and data standards to share best practices of existing smart wearable solutions. This project uses the Medical-Data-Models Portal (MDM Portal) that has evolved to the largest European information infrastructure for medical data models (12). This portal will be used to harmonize and enrich developed data models toward established data standards and foster interoperability with other health information systems. Moreover, active collaboration with the Neurology Department and Task Force on Technology will align clinical and technical key requirements with current ongoing developments.

A 2-year prospective exploratory study is going to be conducted in which the SDS system will be applied within a 20-min data capture session for each included participant. The objective is to train a Deep Neural Network that is capable of predicting the disease entity (PD, ET, none of them) and to identify new phenotypical characteristics based on the fully integrated and pseudonymized study data.

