## Materials and Equipment

The project is planned as a 2-year prospective exploratory study at the Movement Disorders outpatient clinic at the University Hospital Münster. Each patient diagnosed with PD (ICD 10-GM: G20.-) or ET (ICD-10-GM G25.0) and visiting the outpatient clinic is going to be a potential study participant. To be included, each patient must receive, fully understand and sign the informed consent form. All requirements of the updated EU data protection regulation from the start of May 2018 will be strictly adhered to. The study design is registered on Clinicaltrial.gov (Identifier: NCT03638479).

Figure 1 provides an overview of the SDS system and its intended processing steps. Three Apple-based mobile devices will be customized for different monitoring settings. Smartwatch-based examination takes 10-min including calibration and putting them on both wrists. The total assessment time including questionnaires (8 min), drawing one spiral (1–2 min) is 20 min.

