**Figure 1 F1:**
[figure not shown]
Overview of the Smart Device System.

The examiner smartphone (iPhone at least Series 7) constitutes the first step of examination and provides short questionnaires about non-motor symptoms, family history and medication. Two smartwatches (Series 4.0) constitute the second step and enables high-resolution tremor capture from both wrists in a neurological examination (see Table 1). The captured data will be sent via Bluetooth to the smartphone. Since only one smartwatch can be paired with one smartphone at the same time, another smartphone is necessary to forward data from the second smartwatch to the examiner iPhone. The iPad Pro constitutes the final step of the assessment and will enable drawing of Archimedean spirals after protocol-based neurological examination. Captured data will be sent to the examiner smartphone, from which all captured data will be pseudonymized and securely transmitted in JSON format into a European General Data Protection Regulation-compliant research database. This connection to the research database is implemented within a REST-based client-server architecture using HTTPS as encryption. Two exemplary JSON files are attached as Supplementary Files that show structure of the transmitted raw data for two subject cases (one healthy subject, one with Parkinson's disease). The raw data from each JSON file will then be imported into a PostgreSQL-based research database. The overview of all data items is listed in the Table S1. All data processing, transmission, and storage processes were approved by the local data protection officer.

**Table 1 T1:** Smartwatch-based steps of neurological examination.

**Step**	**Duration (s)**	**Description**
1a	20	Rest tremor. Participant is seated in resting position, standardized to Zhang et al. (9)
1b	20	Rest tremor and serial sevens. Participant starts from 100, subtracts 7, and stops after five answers.
2	10	Hold arms lifted.
3	10	Lift and extend arms according to Zhang et al. (9)
4	20	Hold 1 kg weight in every hand for 10 s. Start with the right hand. Then, have the participant's arm rested again as in 1a.
5	20	Finger pointing. Participant should point with his index fingers repetitively to examiner's lifted hand for 10 s. Start with participant's right index, then left.
6	20	Drink from glass. Have the participant grasp an empty glass with his right hand as if he/she would drink from it. Then repeat with his/her left hand.
7	10	Cross and extend both arms.

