8	10	Bring both index fingers to each other, repeat until time expires.
9	20	Let participant's both index fingers tap his/her nose. Repetitively with the right (10 s), then with left index (10 s).
10	20	Entrainment. While holding the arms extended, have the participant stamp with his/her right foot according to the stamp frequency of the examiner. Then have him/her repeat with the left foot.

The software development for smartwatch-based and smartphone-based data capture is already finished. Tablet-based data capture will be included as soon as development and tests are completed. The first 3 months of the study consist of a setting up and testing phase, regardless of the tablet-based component. Only then, patients will be recruited and data capture commences and endures for 21 months. Based on a database report of the local EMR system, we expect 120 patients with ET and 954 patients with PD at our local site. A fixed number of follow up visits is not planned during this study. However, patients that will re-appear at the local site according to the usual treatment plan will be identified as follow-up patients to enable data analysis on disease progression.

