### Data Capture and Neurological Examination

Preceded by a literature review of tremor-related medical history, clinical phenomenology and the new tremor classification (8, 13–18) a series of workshops were conducted with neurologists specialized in Movement Disorders. As a result, a set of questionnaire items and a short technology-based examination were designed to capture data features, which were regarded to have highest predictive power for differential diagnoses of ET and PD. The questionnaire items will be captured first and are listed in Table S1. Then, neurological examination will start with one smartwatch at each participant's wrist, see Table 1. All steps in this examination are illustrated in a video (19) and the examiner initiates the next step or can repeat the current step. Thus, the acceleration data is always labeled with the corresponding examination step, which will provide essential context information for training the Deep-Learning model. The final assessment is to have the participant draw a spiral with a provided stylus and tablet (Figure 2), starting with the right hand and then with left hand. All components of the SDS-system (smartphone, smartwatches, and tablet) will only capture, pseudonymize, and submit data to a research database for Deep Learning. No components of the system will apply any analyses that intends to confirm or change any routine diagnostic or therapeutic procedures. Instead, all advanced data analyses will be conducted subsequently on the pseudonymized data at the research database server and none of analyses results will be sent back to the patient-level.

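### Medication, plausibly a consequence of the diagnosis being predicted, is among the classifier's inputs, so it can inflate KPI 2, and no planned analysis separates it from movement information

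*Protocol article*

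**What the plan says.** - **Medication is captured.** The Introduction lists, as one of three monitoring settings, "Electronic questionnaires regarding medication/drug consumption, family history and non-motor symptoms on a smartphone". Materials and Equipment repeats that the examiner smartphone "provides short questionnaires about non-motor symptoms, family history and medication".
- **It is a model input.** Methods and Anticipated Results says: "The sum of all captured and processed data will train a neural network model to predict the diagnosis label (PD, ET, none of them". The Introduction states the objective as a network that predicts disease entity "based on the fully integrated and pseudonymized study data". Data Capture and Neurological Examination says that questionnaire items and examination were designed to capture features "which were regarded to have highest predictive power for differential diagnoses of ET and PD".
- **The label predates data capture.** Materials and Equipment defines the potential participants as "Each patient diagnosed with PD (ICD 10-GM: G20.-) or ET (ICD-10-GM G25.0) and visiting the outpatient clinic". Performance is calculated against the diagnosis labels that already exist. Controls are healthy companions (Recruitment).
- **Patients are in ongoing care.** Follow-up data come from "patients that will re-appear at the local site according to the usual treatment plan" (Materials and Equipment).
- **The target.** KPI 2 asks for more than 90% accuracy, sensitivity and PPV in classifying ET and PD, under nested cross-validation. It does not name a positive class.

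Nothing in the article removes medication from the inputs, restricts the sample to untreated patients, or ties KPI 2 to a model of movement data.

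**The concern.** An input that follows from the label lets a model recover the label without learning anything about the disease. In a diagnosed outpatient population, the drugs a patient reports plausibly reflect the diagnosis on file. The same applies to patients against healthy companions, who would mostly report no disease-specific drug.

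Three things are at stake.

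1. Reaching the required performance is the stated trigger for medical device approval and rollout to further sites (Interpretation of Anticipated Results). The same section justifies the system by high misdiagnosis rates. A model that leans on prescriptions repeats the existing diagnosis, errors included, and helps little where the patient is not yet diagnosed or treated.
2. The Introduction expects that integrating the data settings will improve classification. Part of any gain could come from the drug list.
3. The planned checks would not show it. The link between drug and diagnosis is present in every fold, so nested cross-validation preserves it. It is a true association with the label, so a permutation test would call it significant. Comparing CNN with LSTM compares architectures, not data sources.

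**Working it through.** **Starting point.** KPI 2 is taken from classification performance in other disease domains and has no derivation to reproduce. The recruitment figure can be checked: 120 ET + 954 PD = 1,074, and half of that is 537 (477 PD, 60 ET), consistent with the stated expectation of at least 500 if every second patient consents.

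**Inputs.** 477 PD and 60 ET, from the document. Assumed, because the documents give no prescribing data: *t*, the share of PD patients on a PD drug, varied; *e*, the share of ET patients on one, 0.02 to 0.05.

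**Two-class rule: on a PD drug means PD, otherwise ET.**

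- PD sensitivity = t
- PD PPV = 477t / (477t + 60e)
- Accuracy = (477t + 60(1 − e)) / 537
- ET PPV = 60(1 − e) / (60(1 − e) + 477(1 − t))

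At t = 0.92, 477t = 438.84 and 477(1 − t) = 38.16.

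- Accuracy: (438.84 + 57)/537 = 0.923 to (438.84 + 58.8)/537 = 0.927
- PD PPV: 438.84/441.84 = 0.993 to 438.84/440.04 = 0.997
- ET PPV: 57/95.16 = 0.599 to 58.8/96.96 = 0.606

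| t | PD sensitivity | PD PPV | Accuracy | ET PPV |
|---|---|---|---|---|
| 0.85 | 85% | 99.3–99.7% | 86.1–86.5% | 44–45% |
| 0.92 | 92% | 99.3–99.7% | 92.3–92.7% | 60–61% |
| 0.95 | 95% | 99.3–99.7% | 95.0–95.3% | about 71% |

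With PD as the positive class, sensitivity is the binding criterion. At t = 0.90 accuracy is already (429.3 + 57)/537 = 0.906 to (429.3 + 58.8)/537 = 0.909, so all three thresholds are passed once t exceeds 0.90.

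**Reference without any data.** Always predicting PD gives accuracy 477/537 = 88.8%, PD sensitivity 100% and PD PPV 88.8%. At t = 0.92 the medication rule adds 3.5 to 3.8 points of accuracy. At t = 0.85 it is less accurate than this guess.

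**What ET requires.** ET PPV above 0.90 needs 477(1 − t) < 60(1 − e)/9, that is t > 1 − 60(1 − e)/(9 × 477). For e = 0.02 this is 1 − 58.8/4,293 = 0.986; for e = 0.05 it is 1 − 57/4,293 = 0.987.

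**Three classes.** Further assumptions: C = 268 or 537 controls; *u*, the share of ET patients on a drug that identifies ET; *x*, the share of controls on that drug; no other cross-over. Patients on neither drug are called control.

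- Accuracy = (477t + 60u + C(1 − x)) / (537 + C)
- ET sensitivity = u
- ET PPV = 60u / (60u + Cx)

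With t = 0.95, u = 0.95 and x = 0, all criteria for PD and ET are met: accuracy is 778.15/805 = 96.7% for C = 268 and 1,047.15/1,074 = 97.5% for C = 537. With x = 0.05, ET PPV falls to 57/(57 + 13.4) = 81% or 57/(57 + 26.85) = 68%, and KPI 2 fails. With u of 0.50 to 0.70, ET sensitivity is 50–70%, and it fails again.

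**The case against.** **The stronger reading.** A reader might infer that KPI 2 can be met from one medication item with no movement information. The documents do not support that. KPI 2 speaks of classifying both ET and PD, and for ET the rule has a PPV of about 60% at t = 0.92 and about 71% at t = 0.95. The planned model has three classes, and there the rule succeeds only under near-ideal prescribing patterns. Much of the apparent accuracy is class imbalance, as the 88.8% from always predicting PD shows. This objection stands, and it limits the claim to inflation of KPI 2.

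**The inputs are uncertain.** The prescribing shares are assumed. That medication follows from the diagnosis is an inference from a diagnosed clinic population. Table S1 is not shown, so it is unknown whether medication is coded by drug, by class or as yes/no. This also stands. It makes the size uncertain, but not the fact that medication is captured and used.

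**The plan is not final.** Stepwise Procedures says that model training will be refined once data are collected. Regression analyses are planned to study the predictive power of input features, and these could show medication dominating. The study is exploratory, returns no results to patients, and advises caution about the KPIs. This helps only in part: regression on the features does not change the model on which KPI 2 is computed, and the caution concerns imperfect prediction and other environments and examiners. The count of 120 input variables under Limitations covers only the smartwatch examination and does not confine the model to movement data.

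**Conclusion.** The concern holds as a risk of bias in the study's headline criterion. As written, the model on which KPI 2 is judged may use medication to predict a diagnosis that plausibly determined the medication, and no planned result would separate that contribution from movement information. Medication need not meet the target alone to matter, because any contribution raises the reported figures.

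The size rests on assumed prescribing shares. In a two-class comparison with PD as the positive class, medication alone passes all three thresholds once just over 90% of PD patients take a PD drug. For ET it does not, short of about 98.6% of PD patients treated. With controls included, it passes for both diseases only under near-ideal assumptions. The article does not say which class or classes KPI 2 treats as positive, so the more permissive reading remains open.

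**What to change.** State in the analysis section that KPI 2 is computed on a model that excludes the medication items. On the same cross-validation folds, report two secondary results, both labelled not diagnostic:

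- the model with medication added;
- a medication-only benchmark.

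The difference between the first and the KPI 2 model shows what medication adds, and the benchmark shows how far medication goes alone. Medication can still be collected and used descriptively.

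The change needs a sentence or two in the plan, a few extra model runs and no new data. Its downside is that the reported performance may be lower.

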## Abstract

Parkinson's disease and Essential Tremor are two of the most common movement disorders and are still associated with high rates of misdiagnosis. Collected data by technology-based objective measures (TOMs) has the potential to provide new promising and highly accurate movement data for a better understanding of phenotypical characteristics and diagnostic support. A technology-based system called Smart Device System (SDS) is going to be implemented for multi-modal high-resolution acceleration measurement of patients with PD or ET within a clinical setting. The 2-year prospective observational study is conducted to identify new phenotypical biomarkers and train an Artificial Intelligence System. The SDS is going to be integrated and tested within a 20-min assessment including smartphone-based questionnaires, two smartwatches at both wrists and tablet-based Archimedean spirals drawing for deeper tremor-analyses. The electronic questionnaires will cover data on medication, family history and non-motor symptoms. In this paper, we describe the steps for this novel technology-utilizing examination, the principal steps for data analyses and the targeted performances of the system. Future work considers integration with Deep Brain Stimulation, dissemination into further sites and patient's home setting as well as integration with further data sources as neuroimaging and biobanks. Study Registration ID on ClinicalTrials.gov: NCT03638479.

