## Interpretation of Anticipated Results

### Results

Each of the three technology-driven data capture settings is expected to show high potential to classify tremor-related diseases. Synchronization of these multimodal data and integrative pattern recognition analyses are expected to provide deeper insights into tremor characteristics. All of the technical devices used within this study have recently evolved to affordable mass products. Coupled with highly customizable apps, some of these devices already received FDA approval as for instance the Kardiaband app by AliveCor, the first FDA-cleared smartwatch-based ECG reader (22). This demonstrates the qualified use of such smart wearables not only for fitness or wellness purposes but also for valid medical use. A further advantage of the SDS system—compared to commercial and proprietary systems as the KinetiGraph™ system—is that all of its devices can be programmed and adapted by any Apple-based App developer through well-established Software Development kits and therefore preventing vendor lock-in. Once our system has reached the required level of accuracy, sensitivity and precision, regulatory steps will be taken for medical device approval and rollout to further sites. As a consequence, the system will not replace but could decisively extend diagnostic processes, which are currently suffering from high misdiagnoses rates in this domain (2, 3).

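### KPI 2 is scored against the existing clinic diagnosis, so reaching it shows agreement with that diagnosis and not better diagnosis

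*Protocol article*

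**What the plan says.** **Label.** Materials and Equipment defines the patients by their diagnosis at entry: "Each patient diagnosed with PD (ICD 10-GM: G20.-) or ET (ICD-10-GM G25.0) and visiting the outpatient clinic" is a potential participant. Methods and Anticipated Results then fixes the truth standard: sensitivity, PPV and accuracy "will be calculated based on existent diagnosis labels using nested cross-validation". I read these labels as the diagnoses with which patients enter. The article describes no independent, blinded or follow-up-confirmed reference diagnosis.

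**Target.** KPI 2 in the same section is ">90% accuracy, >90% sensitivity, >90% positive predictive value for classifying ET and PD by the tested model using nested cross validation".

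**Motivation and conclusion.** The Abstract says that the two disorders "are still associated with high rates of misdiagnosis". The Results part of Interpretation of Anticipated Results makes the required performance the trigger for seeking device approval and rollout to further sites. It then says that, as a consequence, the system would not replace but "could decisively extend diagnostic processes, which are currently suffering from high misdiagnoses rates in this domain".

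**Caveats given.** Limitations asks for caution even if the targets are met, because prediction is never flawless and because examiners and environments differ. It does not mention error in the diagnosis labels.

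**The concern.** The yardstick for the model is the routine diagnosis whose unreliability is the reason for the study. Measured this way, accuracy is agreement with current practice. Nested cross-validation and permutation tests do not change that: the same labels are used in the training and test folds, and the permutation test asks only whether predictions are related to those labels.

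Two misreadings follow. Meeting KPI 2 could be taken as evidence that the system helps with misdiagnosis, although a model that has learned the clinic's errors would meet it best. Missing KPI 2 could be taken as model failure when part of the shortfall is label error. The second risk is largest for ET, because ET is the small class: a small share of the many PD labels is a large number beside the ET cases.

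**Working it through.** **Inputs from the article.** Expected patients: 954 PD and 120 ET (Materials and Equipment). Consent in every second patient (Limitations). Target above 90% (KPI 2).

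**The plan's own figure.** (954 + 120)/2 = 537, which fits the article's expectation of at least 500 patients. By class, 954/2 = 477 labelled PD and 120/2 = 60 labelled ET. KPI 2 itself is a benchmark taken from other disease domains, so it has no formula to reproduce.

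**Assumed inputs.** The article gives no label error rate. Let *a* be the share of PD labels that are truly ET, and *b* the share of ET labels that are truly PD. Controls are left out.

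**A classifier that is always right, scored against the labels:**

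- ET sensitivity = 1 − b
- ET PPV = 60(1 − b) / [60(1 − b) + 477a]
- Accuracy = 1 − (477a + 60b)/537

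| a | b | ET sensitivity | ET PPV | Accuracy |
|---|---|---|---|---|
| 2% | 10% | 90% | 54/(54 + 9.54) = 85.0% | 1 − 15.54/537 = 97.1% |
| 5% | 5% | 95% | 57/(57 + 23.85) = 70.5% | 1 − 26.85/537 = 95.0% |
| 5% | 20% | 80% | 48/(48 + 23.85) = 66.8% | 1 − 35.85/537 = 93.3% |

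**Break-even for ET PPV.** Suppose every ET label is correct. Six truly-ET patients among the 477 labelled PD give 60/66 = 90.9%. Seven give 60/67 = 89.6%, below target. Seven of 477 is about 1.5%.

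**PD side, for balance.** In the first row, PD sensitivity is 98% and PD PPV is 467.46/(467.46 + 6) = 98.7%. The effect falls almost wholly on ET.

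**What 90% agreement says about true accuracy.** In the two-class setting with overall label error *e* and agreement 0.90, true accuracy lies between 0.90 − e and 1 − |0.10 − e|:

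| Assumed e | True accuracy can be |
|---|---|
| 5% | 85–95% |
| 10% | 80–100% |
| 15% | 75–95% |
| 20% | 70–90% |
| 25% | 65–85% |

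A model that copies the labels scores 100% and is truly correct in 1 − e. A perfect model scores 1 − e, so it misses the accuracy target once e reaches 10%.

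**The case against.** **The study is exploratory and its claims are hedged.** The article says that concrete hypotheses are limited, asks for caution about the KPIs, and uses conditional language about diagnosis. A reader might infer that it promises fewer misdiagnoses; it does not say so. This softens the point, but the hedges concern imperfect prediction and new settings, not the labels, and device approval is still tied to these targets.

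**The site is a movement disorders clinic.** The statements about misdiagnosis concern the disorders and the field in general. A reader might infer that this clinic's diagnoses are often wrong, and nothing in the article shows that. This stands, and it is why the error rates above are assumptions. The break-even of about 1.5% shows that even a low rate matters for ET PPV.

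**KPI 2 may not be meant per class.** The article does not say whether each target applies to ET separately. If only overall figures count, the assumed scenarios leave a perfect model above 90% accuracy. This also stands and limits the numerical part, though not what KPI 2 measures.

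**Label details may sit in the full protocol or analysis plan.** That is fair for label dates and handling of changed diagnoses, so their absence is not criticised. The reference standard and the conclusion drawn from it are stated in the article.

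**The phone display.** A reader might see a contradiction between devices that "will only capture, pseudonymize, and submit data to a research database for Deep Learning" and a figure showing "visualization of average amplitude and frequency, raw acceleration data during examination section 3 and frequency spectrum", and infer that the examiner's view, or the option to repeat a step, could contaminate the labels. The documents do not support this. The same section (Data Capture and Neurological Examination) goes on to bar analyses meant to confirm or change routine care, and it places advanced analyses on the server with nothing returned to patient level. The figure shows descriptive signal values for a simulated case. Patients enter already diagnosed, and nothing links the display or a repeated step to a label.

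**Conclusion.** The point holds as one about the reference standard. KPI 2 can show how closely the model agrees with the clinic's diagnosis. It cannot show that the model diagnoses better, so the move from reaching the targets to helping an error-prone diagnostic process does not follow from it.

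The possible distortion is large for ET PPV and small for overall accuracy. The sizes rest on assumed error rates, on half of the expected patients consenting, on a two-class comparison without controls, and on reading KPI 2 per class. What KPI 2 measures depends on none of these assumptions. The change is worth making because it alters what the study can conclude.

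**What to change.** 1. Keep the entry diagnosis as the label and store it before the session. A later diagnosis should not replace it, since that would be set after the measurements.
2. Word KPI 2 and the conclusion from it as agreement with the clinic diagnosis.
3. Name label error in Limitations, with its two effects: copied errors are rewarded and correct predictions can be penalised.
4. In the Results part of Interpretation of Anticipated Results, remove the step from reaching the targets to remedying misdiagnosis.
5. Add one sensitivity analysis: KPI 2 in patients whose diagnosis was re-confirmed at a return visit. Materials and Equipment already provides for identifying returning patients. No fixed follow-up is planned, so patients who never return must not count as confirmed merely because their record is unchanged.

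The cost is a stored entry field, one small analysis and a more modest conclusion; no extra assessor is needed. The re-confirmed patients are a selected subset and re-confirmation is not proof of the true diagnosis, so this analysis supports the main result without replacing it.
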